#### Coordination tests on a balance platform

The coordination test is based on quantitative posturography on a force platform (HUR Smart balance, HUR, Finland) and consists of a static and a dynamic exercise. For the static tests, participants remain motionless in upright standing position (heels 2 cm apart, toes pointing outwards as indicated on the platform, 30° angle) with open eyes for 30 s. Subsequently, the same test is performed with eyes closed. Thereafter, the test is repeated on an instable ground (foam mat), with eyes open as well as with eyes closed.

The dynamic test (Limits of stability test) is performed with the feet in parallel position in a hip wide stance (indicated on the platform). The participants have to bend as far as possible forward, backward, left and right without moving or lifting the feet off the platform. Quantitative measurement of postural sway can be used to predict falls in older people [36].

#### 6-Minute-walk-test

To assess the cardio-pulmonary capacity, a 6-Minute-Walk-Test (6MWT) is performed [37, 38]. For this, the participants are asked to walk for 6 min on a 30 m course at a self-paced speed but as rapid and safe as possible. The distance walked within 6 min is documented for each participant. The use of an assistive device (e.g. cane or walker) is allowed and documented.

#### Grip strength

Low grip strength serves as an indicator for an augmented mortality [39]. Grip strength is measured with a hydraulic hand dynamometer (JAMAR, Patterson Medical, USA) in a sitting position. Participants are holding their forearm perpendicular to the upper arm and squeeze the handle of the dynamometer as hard as possible. The test is performed twice and the maximal strength is documented.

#### Fear of falling—Short falls-efficacy-scale – international

To assess the fear of falling, the short form of the Falls-Efficacy-Scale—International (short FES-I) is used. The international questionnaire has been validated for the German language and provides information on level of concern about falls for seven typical activities of daily living with four answer options (1 = not at all concerned to 4 = very concerned) [40].

#### Quality of life – WHO-5 well-being index

Mental and physical health are assessed by the WHO-5 Well-Being Index (WHO-5). The WHO-5 questionnaire comprises five statements to assess subjective mental well-being over the past two weeks. Answer categories are “At no time = 0 point” to “All of the time = 5 points “. The scores of all questions will be summarised and the score then multiplied by 4. The final score ranges from 0 (lowest well-being index) to 100 (highest well-being index) [41].

#### Sarcopenia – SARC-F-questionnaire

The SARC-F-questionnaire is a valid tool for identifying individuals at risk for adverse outcomes from sarcopenia. The SARC-F-questionnaire comprises five items: Strength, assistance with walking, to rise from a chair, to climb stairs and falls with 0 to 2 points for each component resulting in a summary score from 0 to 10 points. A score ≥ 4 points is an indicator for sarcopenia [42]. Further assessments (e.g. grip strength, chair stand test, BIA and SPPB) can be used to quantify sarcopenia, according to official recommendations [8].

#### Nutritional status—Mini nutritional assessment

People over 65 years are often at risk of malnutrition, a condition which also promotes sarcopenia and frailty. To assess the nutritional status the short form of the Mini Nutritional Assessment (MNA®-SF, https://www.mna-elderly.com), a well validated screening tool in many care settings, is used. The instrument comprises six questions to screen for the risk of malnutrition (12–14 points: normal nutritional status; 8–11 points: at risk of malnutrition; 0–7 points: malnourished) [43].

#### Physical activity

Current physical activity is assessed regarding regular current type of activity e.g. walking, bicycling, gymnastics, swimming, duration performed per week and accompanying intensity. The latter is defined by Metabolic Equivalent Tasks (MET) according to Ainsworth et al. [44].

Moreover, former physical activity during lifetime will be assessed according to age and type of sport performed as well as weekly exercise sessions (Additional file 1: Supplement).

#### Activities of daily living

Activities of daily living (ADL) is assessed by the Barthel-Index, which includes 10 questions to assess function and to detect problems in performing activities of daily living, as well as the degree of assistance required with scores from 0 points (difficulties in ADL) to 10 points (no difficulties) with a total score of 100 points. The questions comprise activities such as feeding, personal toileting, bathing, dressing/undressing or control of bladder and bowel. A higher score is associated with a greater degree of independence [45].

#### Cognition test – Montreal cognitive assessment

To assess signs of dementia, the Montreal Cognitive Assessment (MoCA) is to be applied. The 30-points test assesses several cognitive domains including short-term memory, visuospatial abilities, executive functions, attention, concentration and working memory, language and orientation to time and place. The score ranges from 0 to 30 points with lower scores indicating cognitive impairments [46].

MoCA is also used to evaluate the validity of questionnaires. If MoCA score is below 10 points, all other questionnaires will not be considered for evaluation.

### Adverse and serious adverse events

The process evaluation comprises the documentation of recruitment rate and drop-out as well as lost-to-follow-up rate, the documentation of adherence to the training, and the documentation of adverse events (AEs) due to training (complaints while and immediately after training) and serious adverse events (SAEs).

AEs are defined as: Clinical events that occur during the training session or may possibly be related to the training intervention including accidents that occur during the training session or may possibly be related to the training intervention.

SAEs are defined as death, life-threatening events, events that lead to permanent damages or invalidity, or events that are followed by over-night hospitalisation.

AEs due to training and SAEs that occur during the study period irrespective of group assignment are documented in safety forms and transferred to a safety data base. In case of an SAE the principal investigator is directly informed and the procedure on further participation of the study determined e.g. study end, adaptations of the training, temporary or complete cessation of the training.

Throughout the course of the bestform trial, SAEs can be differentiated according to cardiovascular events and analysed separately. MACE are cardiovascular death, non-fatal stroke, and non-fatal myocardial infarction (3-point MACE). MACE and all-cause mortality will be documented during the study and the follow-up phase.

A questionnaire for falls documentation is used at the examinations ex1-ex3, in which the falls and fall-related injuries of the participants are recorded (Additional file 1: Supplement). A falls diary is not applied. Additional documentation is carried out by staff of the senior care facilities or by the trainers in the intervention care facilities (Table 2).

All participants are followed until end of study. A list of SAEs is provided to the responsive Ethics Committee after the end of the study.

### Data monitoring

Monitoring of the study data is performed by the Münchner Studienzentrum (MSZ), Munich, Germany, an independent institution experienced in the monitoring of clinical studies in accordance with standard operating procedures of the MSZ to ensure patients´ safety and integrity of the clinical data, e.g. primary outcome measure and adherence to the study protocol. Monitors have at all times access to all essential documents of the study. All study information is provided to the monitoring personnel during visits. Monitoring procedures are predefined in a study-specific monitoring plan. Furthermore, at the end of the clinical study, a close-out visit is planned to address all activities required for adequate study finalisation.

### Blinding

The primary endpoint is assessed in a blinded manner by independent test personnel. Study participants and physicians, who conduct medical examinations are not informed about the group allocation of the study participants. Secondary endpoints are also partially assessed by unblinded personnel.

### Statistical analysis

#### Sample size calculation – Number of participants

For the primary analysis, mean values in changes of the SPPB score are compared between study groups accounting for the cluster-randomised design. We hypothesise that the intervention group could present at least a difference in mean changes of one point compared to the control group, which is considered as clinically relevant [47, 48]. A within group standard deviation of 2.5 points is assumed [49, 50], translating to an effect size (Cohen’s d) of d = 0.4.

Under these assumptions, 100 participants are needed per group in an individually randomised trial (significance level of 5%, power of 80%, two-sided test). Assuming a mean cluster size of 25 participants and an intra-cluster-correlation (ICC) of 0.025 [51, 52], this sample size has to be multiplied by a Design Effect (DE) of 1.6 to account for the cluster-randomised setting [53], resulting in a sample size of 160 participants per group. As we assume that about 20% of the included individuals will not provide data at the six months assessment, the sample size is increased to 400 individuals in total. To achieve this  ≥ 20 senior care facilities is planned to be recruited.

For the primary analysis comparing the mean values of changes in the SPPB score between the study groups, a mixed effects linear regression model with fixed effect for study group and baseline SPPB score and random cluster effects (senior residences) will be fitted to the data in order to account for within cluster correlation introduced by the cluster-randomised design [54]. The estimated mean difference between the study groups will be represented by the estimated regression coefficient for study group. The null hypothesis of no group difference will be tested two-sided on a significance level of α = 0.05 and a 95% confidence interval for the difference between group mean values will be estimated and presented. Means and standard deviations for both groups will be shown.

Secondary endpoints will be analysed in an exploratory manner. For continuous data, observed means and standard deviations will be presented for both study groups and tests for group differences will be performed as described for the primary analysis. Absolute and relative frequencies for both groups will be presented for binary outcomes. Group comparisons will be conducted by fitting marginal logistic regression models with study group as independent variable to the data accounting for within cluster correlations (generalised estimating equation, GEE models). For count data (e.g. number of falls) corresponding Poisson regression models or negative binomial models will be used. Kaplan–Meier curves will be drawn to illustrate distributions of time-to-event data (time to first MACE) for both study groups. For group comparisons, a Cox regression model with fixed effect for study group and robust standard errors considering the clustering will be fitted to the data. Estimated hazard ratios with corresponding 95% confidence intervals will be presented. Observed adverse events and serious adverse events will be listed and frequencies of adverse events and serious adverse events will be presented. Proportions of individuals with at least one adverse event will be compared between study groups using a logistic GEE model accounting for clustering.

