### Recruitment of senior care facilities

Senior care facilities are recruited in the Munich area. A local media campaign and personal telephone calls to senior care facilities will draw attention to the study. A total of 20 senior care facilities is projected, but if the aimed number of participants of  ≥ 400 is not reached, then further facilities will be included until this number is met. Eligibility criteria for senior care facilities include adequate space for implementing exercise facilities and commitment of the general manager of the senior care facility to take part in the study. Study sites include senior homes, offering assisted living as well as caring areas covering the whole spectrum of level of care. Senior care facilities are advised that participation into the trial does not automatically imply participation into the intervention arm. Aside, senior care facilities should preferably have  ≥ 100 residents and an expected participation rate  ≥ 20 residents. Furthermore, no regular machine-based strength training should have been installed. However, care facilities should have the space to set up a fitness facility for a machine-based exercise training programme.

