### Primary outcome

Primary outcome is the change of physical function between baseline and after six months of intervention, measured as the Short Physical Performance Battery (SPPB), a summary performance score out of three tests (standing balance test, gait speed test, and Chair-Stand-Test). For each participant the difference between six months to baseline will be used for analysis.

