### Examinations and assessments

The following examinations are planned at baseline (ex1), after three months (ex2) and after six months (ex3) of the intervention on an individual basis. Echocardiography, the coordination test on a balance platform, and the Montreal Cognitive Assessment (MoCA) [28] will only be assessed at ex1 and ex3. Questionnaires are conducted by interview by trained study staff.

A follow-up questionnaire (Serious adverse events (SAEs), Major adverse cardiac events (MACE) [29], falls, fall-related injuries, care degree) is planned after 18 and 30 months.

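### The primary model adjusts for baseline SPPB alone and so forgoes a modest, nearly free gain in precision from other baseline predictors

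*Protocol article*

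**What the plan says.** The model is stated in the article under Sample size calculation – Number of participants: a mixed effects linear regression "with fixed effect for study group and baseline SPPB score and random cluster effects", where the clusters are the facilities. The group coefficient is "tested two-sided on a significance level of α = 0.05". The response is the change score: under Primary outcome, "For each participant the difference between six months to baseline will be used for analysis". The covariate set is therefore fixed, not left open.

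Three other places bear on it:

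- **Facility mix.** Recruitment of senior care facilities projects 20 facilities and says "Study sites include senior homes, offering assisted living as well as caring areas covering the whole spectrum of level of care".
- **Allocation.** Allocation of senior care facilities describes permuted blocks, 1:1, and names no stratification factor.
- **Baseline data.** Under Examinations and assessments, "the Montreal Cognitive Assessment (MoCA) [28] will only be assessed at ex1 and ex3", and ex1 is the baseline visit. In the section of that name, "Activities of daily living (ADL) is assessed by the Barthel-Index", and Secondary outcomes compares later Barthel values with baseline.

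**The concern.** With about 10 facilities per arm and a setting that runs from assisted living to full care, resident mix will tend to cluster by facility and can differ between arms by chance. Two residents with the same baseline SPPB but different age or cognition may well change differently over six months. Baseline SPPB does not capture that part of the outcome variance, so in the planned model it stays in the residual and facility terms.

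Two things are at stake: the width of the confidence interval, and how far a realised imbalance could push the one estimate obtained. Individual-level covariates spend no facility-level degrees of freedom, so the usual reason for a sparse model with few clusters does not apply to them.

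**Working it through.** **1. The plan's own figure.** Inputs from the sample size section: "at least a difference in mean changes of one point compared to the control group", SD 2.5, two-sided 5%, power 80%, cluster size 25, ICC 0.025, 20% without six-month data.

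- Individually randomised: n = 2 × (1.960 + 0.842)² × 2.5² / 1² ≈ 98.1, so 99 per group. The t-test version gives 99.08, so 100, as stated.
- Design effect: 1 + 24 × 0.025 = 1.6. Then 100 × 1.6 = 160 per group.
- Dropout: 160 / 0.8 = 200 per group, 400 in total.

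The stated size reproduces and takes no credit for any covariate.

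**2. Power of the planned model.** 400 × 0.8 = 320 completers in 20 facilities is 16 per facility and 160 per arm.

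SE = 2.5 × √[2 × (1 + 15 × 0.025) / 160] = 2.5 × √(2 × 1.375 / 160) = 0.328

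With t on 20 − 2 = 18 df, power for 1 point is 82%. This treats 2.5 as the SD left after baseline SPPB.

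**3. Gain by formula.** Let R² be the share of that remaining variance explained by added covariates. The article gives no value, so 0.02 to 0.10 is an assumption. Replace 2.5 by 2.5 × √(1 − R²) and hold the ICC at 0.025:

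| R² | SE | Power (18 df) | Total N by the article's route |
|---|---|---|---|
| 0 | 0.328 | 82% | 398 |
| 0.02 | 0.325 | 83% | 390 |
| 0.05 | 0.320 | 84% | 378 |
| 0.10 | 0.311 | 86% | 358 |

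The first row shows 398, not 400, because it starts from 99 per group.

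**4. Gain when the covariate clusters.** Simulation used 20 facilities × 16 completers, residual ICC 0.025, assumed covariate ICC 0.10 and 8,000 runs per setting. Facility means were analysed with t on 18 df, standing in for the mixed model at equal cluster sizes.

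| R² | SE without → with | Power without → with |
|---|---|---|
| 0.05 | 0.335 → 0.320 | 80.0% → 83.6% |
| 0.10 | 0.343 → 0.315 | 79.7% → 85.9% |

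The gain is larger here because an omitted clustered covariate raises the outcome ICC. At R² 0.10 the ICC becomes 0.9 × 0.025 + 0.1 × 0.10 = 0.0325, and SE = 2.5 × √[2 × (1 + 15 × 0.0325) / 160] = 0.341, close to the simulated 0.343.

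**5. Bias check.** In the same simulation, with R² from 0.05 to 0.20 and the covariate omitted, the mean estimate was 0.99 to 1.00 for a true difference of 1, and −0.00 to 0.005 for a true 0. Type I error was 5.1% to 5.3%.

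**6. Size of a realised imbalance.** The arm difference in a standardised covariate has SD √[2 × (1 + 15ρ) / 160]. This is 0.131 at covariate ICC ρ = 0.025 and 0.177 at ρ = 0.10, so a gap above 0.2 SD arises in about 13% to 26% of trials per covariate. The slope per SD is 2.5 × √R²: 0.35 points at R² 0.02 and 0.79 at 0.10. A 0.2 SD gap then moves the SPPB-only estimate by about 0.07 to 0.16 points, or 0.2 to 0.5 of the SE of 0.328.

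**The case against.** The strongest reply is that nothing here is wrong. The model is pre-specified, includes the baseline value of the outcome, accounts for clustering, and meets its power target without further covariates. That stands.

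A reader might go further than the article allows in three ways:

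- **That the SPPB-only model is biased.** It is not. Chance imbalance is part of the sampling variance that the SE, the test and the interval already cover (step 5). Systematic imbalance would need another mechanism, such as residents enrolling once the allocation is known; that is a separate question and does not follow from the choice of covariates.
- **That the estimate is off by a large share of the 1-point target.** Imposing a 0.3 SD gap and a slope of 0.4 to 0.8 points per SD gives 0.12 to 0.24 points. The article supplies neither figure. With an assumed covariate ICC of 0.1 to 0.2 (chance SD about 0.17 to 0.22), a gap that large arises in only about 8% to 17% of trials, and the shift is still 0.4 to 0.7 of the SE.
- **That planned precision is lost.** The sample size never counted on it; a possible gain is forgone.

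Further objections carry some weight. Eligibility requires independent standing and excludes dementia that rules out small-group training, which narrows the range of function and cognition and favours the lower R² values. The article names no stratification factor, which is not a statement that none is used, and the full protocol or analysis plan may list more covariates. Finally, the Blinding section says secondary endpoints are partly assessed by unblinded staff. MoCA is one of them, so it should be confirmed that its baseline value is protected; age and sex are not exposed to this.

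**Conclusion.** The point holds as a recommendation. The primary analysis is valid but leaves out baseline predictors that would probably sharpen it at very little cost. The gain is about 1 to 4 power points by formula for an assumed extra R² of 0.02 to 0.10, and about 4 to 6 points in simulation for R² 0.05 to 0.10 with a covariate ICC of 0.10. Its true size is unknown.

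These figures rest on 20 facilities with 16 completers each, an SD of 2.5 after baseline SPPB, and a residual ICC of 0.025. The downside is small: in a further simulation (ICC about 0.02, 4,000 runs), a covariate of no predictive value changed power by less than half a point (0.856 against 0.854). There is no bias, no inflated error rate and no contradiction to correct.

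**What to change.** In the primary analysis paragraph, add age, sex and baseline MoCA as individual-level fixed effects, chosen before any outcome data are seen, with a simple stated rule for the few missing baseline values. Keep the SPPB-only model as a sensitivity analysis.

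Do not add baseline Barthel as things stand. The MoCA section sets aside all other questionnaires when MoCA is below 10, and the Barthel-Index is recorded by questionnaire. It would therefore be missing systematically for the most impaired residents, and mean imputation would assign them average daily function. Include it only if the baseline value is exempted from that rule.

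The cost is a sentence or two in the plan, one missing-covariate rule and slightly more analysis work. MoCA is already collected. Age must be known for eligibility and sex is almost certainly recorded, though the text at hand does not list either as a baseline item.

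### The stated count model for falls has study group as its only term, although falls are recorded at baseline: an avoidable loss of precision in an exploratory endpoint, not a bias

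*Protocol article*

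**What the plan says.** All of this is in the protocol article.

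- **Primary model** (Statistical analysis): "a mixed effects linear regression model with fixed effect for study group and baseline SPPB score and random cluster effects".
- **Continuous secondary endpoints** (same section): "tests for group differences will be performed as described for the primary analysis". They therefore take over the baseline term.
- **Binary endpoints** (same section): group comparisons are made by "fitting marginal logistic regression models with study group as independent variable to the data accounting for within cluster correlations", using GEE.
- **Counts** (same section, directly after the binary endpoints): "For count data (e.g. number of falls) corresponding Poisson regression models or negative binomial models will be used". No model terms are listed in this sentence.
- **Falls endpoint** (Secondary outcomes): the number of falls and of fall-related injuries over six months. Most other items in that list are defined as change from baseline; this one is not.
- **Falls data** (Adverse and serious adverse events): "A questionnaire for falls documentation is used at the examinations ex1-ex3, in which the falls and fall-related injuries of the participants are recorded". Examinations and assessments defines ex1 as the baseline examination: "The following examinations are planned at baseline (ex1), after three months (ex2) and after six months (ex3) of the intervention".

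**The concern.** The trial collects each resident's fall history before the intervention, and the stated falls analysis makes no use of it. It enters neither as a covariate nor through a change score. For continuous outcomes the same section does use the baseline value, and it gives no reason for the difference.

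The setting is one where a baseline count can help. Recruitment of senior care facilities projects about 20 facilities covering the whole range of care levels. Allocation of senior care facilities uses 1:1 permuted blocks and names no stratification factor. The Background describes falls as leading to a further rise in fall risk, which suggests that past falls predict later ones. The Discussion calls the effect of exercise on falls in care facilities uncertain. At stake is a wider interval for the falls rate ratio than the collected data allow.

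**Working it through.** **1. The plan's own figures.** No figure is stated for falls. The primary sample size reproduces and supplies the number of residents used below.
- Per arm: 2 × (1.96 + 0.84)² × 2.5² / 1² ≈ 98.1, so 99; a t-based calculation gives 99.1. Stated: 100.
- Design effect: 1 + (25 − 1) × 0.025 = 1.6, and 100 × 1.6 = 160 per arm.
- Dropout: 320 / 0.8 = 400.
- Evaluable residents per facility: 400 × 0.8 / 20 = 16.

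The present point does not touch this sample size.

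**2. Is baseline fall history used anywhere?**

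| Outcome type | Stated terms | Baseline value used? |
|---|---|---|
| Primary (SPPB change) | group, baseline SPPB, random facility effect | yes |
| Continuous secondary | as primary | yes |
| Binary secondary | group, GEE | none stated |
| Counts (falls) | corresponding to the preceding model | none stated |

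The baseline falls record exists (ex1), but no section brings it into the falls comparison.

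**3. Size under assumptions.** The article gives no fall rate, dispersion, between-facility variance or correlation of falls over time, so all of these are assumed. The quantity compared is the variance of the estimated log rate ratio with study group only and with study group plus the log of the baseline count (after adding a small constant). There are 20 facilities of 16 residents, 10 per arm, and the baseline recall window is taken as equal to the six-month follow-up.

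*Log-normal fall-proneness* (log-scale variance 1.0 between residents and 0.1 between facilities; mean 0.5 or 0.8 falls per six months):

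| Correlation of fall-proneness, baseline to follow-up | Cut in variance of log rate ratio |
|---|---|
| 0 | about 1–2% |
| 0.3 | about 7–11% |
| 0.6 to 0.8 | about 14–33% |
| 1.0 | about 30–51% |

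*Gamma fall-proneness* (mean 0.5 falls with dispersion 1 or 2 and between-facility log-SD 0 or 0.3; mean 1.0 with dispersion 1 and log-SD 0). Persistence here is the share of residents who keep the same fall-proneness:

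| Persistence | Cut in variance of log rate ratio |
|---|---|
| none | about 0–2% |
| half | about 2–16% |
| full | about 11–39% |

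The two models agree in direction and in the null case. The gamma model puts the low end at half persistence nearer 2% than 7%.

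**4. What this means for the interval.** On the log scale the width changes by √(1 − cut). A 7% cut gives √0.93 = 0.96 (4% narrower), a 33% cut gives √0.67 = 0.82 (18% narrower), and a 50% cut gives √0.50 = 0.71 (29% narrower).

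**5. Does the target change?** With a true rate ratio of 0.60 (log −0.51), the mean estimated log rate ratio was −0.51 to −0.52 with and without adjustment. This is expected, because a rate ratio under a log link is collapsible.

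**6. Chance imbalance.** Across the gamma scenarios the log ratio of baseline fall rates between arms had an SD of about 0.155 to 0.272. The 95% range of that ratio is exp(±1.96 × 0.155) = 0.74 to 1.35 at the low end and exp(±1.96 × 0.272) = 0.59 to 1.70 at the high end.

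**7. Fall-related injuries.** With an assumed mean of 0.12 injuries per resident, adjusting for the baseline count of the same event cut the variance by only about 0–7% and gave essentially no gain in power.

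**The case against.** **The article may leave covariates to an analysis plan that is not shown.** The count sentence lists no terms, so the group-only reading depends on the word that ties it to the logistic model, and that word could carry over only the handling of clustering. This stands in part: nothing in the article forbids a covariate. But the article names study group as the independent variable in the model that counts follow, and it names the baseline term where it wants one. The point is therefore about a stated choice, not about missing detail.

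**An unadjusted comparison of randomised facilities is valid.** This stands in full. A reader might infer from the imbalance range above that the falls result would be biased. The documents do not support that: chance imbalance is part of the sampling error that a cluster-aware standard error already reflects.

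**The endpoint is exploratory and has no power target.** This also stands. A reader might infer that the trial's stated aim on fall risk is left unadjusted. However, Secondary outcomes measures risk of falling by the Timed-Up-and-Go-Test and the balance platform, and these continuous outcomes do receive baseline adjustment. The number of falls is a separate item.

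**The size depends on favourable inputs.** Without persistence there is almost no gain. The baseline recall window is in a supplement not shown, the baseline count is recalled at interview, and facility staff or trainers supply additional fall documentation, so baseline and follow-up may not be fully like for like. Any of these could shrink the gain. The figures come from Poisson models; the negative binomial alternative was not tried. I quote no power gain, since the plan sets no target and the fall rate and effect would both have to be assumed.

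**Conclusion.** The point holds as a matter of efficiency. As stated, the falls model omits a baseline count that the trial already collects, while the primary and continuous secondary models use theirs. Under the assumed 0.5 to 0.8 falls per six months in 20 facilities of 16 residents, adjustment would cut the variance of the log rate ratio by about 0–2% without persistence, about 7–33% at low to strong persistence, and up to about 50% at full persistence. The gamma model's low end at half persistence is about 2%. The rate ratio estimated is the same either way, and in the null case adjustment cost essentially nothing.

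The documents do not support calling the falls analysis invalid or biased, nor extending these figures to fall-related injuries. The primary analysis is unaffected. It is a modest improvement worth making before the data are seen.

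**What to change.** In the secondary-endpoint paragraph of Statistical analysis, or in the analysis plan, state that the count model for falls includes study group and the resident's ex1 number of falls, for example as log(count + 1), with the planned handling of clustering. Report the unadjusted rate ratio alongside. Other functional forms of the baseline count would also serve; what matters is fixing one in advance, because a covariate added after an imbalance is seen invites a charge of selective adjustment.

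For fall-related injuries, use the ex1 number of falls as the covariate as well, since the ex1 injury count is too sparse to help much, and claim no quantified gain.

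The cost is one or two sentences, with no new data, visits or staff. The downsides are small: recall error at ex1 reduces the benefit, and a simple rule is needed for residents with no baseline count.
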